# IMPACT study on intervening with a manualised package to achieve treatment adherence in people with tuberculosis: protocol paper for a mixed-methods study, including a pilot randomised controlled trial

**DOI:** 10.1136/bmjopen-2019-032760

**Published:** 2019-12-17

**Keywords:** tuberculosis, medication adherence, manuals, protocols & guidelines, pilot studies

## Abstract

**Introduction:**

Compared with the rest of the UK and Western Europe, England has high rates of the infectious disease tuberculosis (TB). TB is curable, although treatment is for at least 6 months and longer when disease is drug resistant. If patients miss too many doses (non-adherence), they may transmit infection for longer and the infecting bacteria may develop resistance to the standard drugs used for treatment. Non-adherence may therefore risk both their health and that of others. Within England, certain population groups are thought to be at higher risk of non-adherence, but the factors contributing to this have been insufficiently determined, as have the best interventions to promote adherence. The objective of this study was to develop a manualised package of interventions for use as part of routine care within National Health Services to address the social and cultural factors that lead to poor adherence to treatment for TB disease.

**Methods and analysis:**

This study uses a mixed-methods approach, with six study components. These are (1) scoping reviews of the literature; (2) qualitative research with patients, carers and healthcare professionals; (3) development of the intervention; (4) a pilot randomised controlled trial of the manualised intervention; (5) a process evaluation to examine clinical utility; and (6) a cost analysis.

**Ethics and dissemination:**

This study received ethics approval on 24 December 2018 from Camberwell St. Giles Ethics Committee, UK (REC reference 18/LO/1818). Findings will be published and disseminated through peer-reviewed publications and conference presentations, published in an end of study report to our funder (the National Institute for Health Research, UK) and presented to key stakeholders.

**Trial registration number:**

ISRCTN95243114

**Secondary identifying numbers:**

University College London/University College London Hospitals Joint Research Office 17/0726.

National Institute for Health Research, UK 16/88/06.

Strengths and limitations of this studyPatient-centred, mixed-methods approach, based on a robust understanding of the evidence on social, cultural and personal factors that influence adherence to medication to treat tuberculosis (TB).Evidence and experience of adherence captured from a variety of perspectives from across the UK, including patients, their carers and healthcare workers.Generalisable patient population of individuals at risk of non-adherence across low TB incidence settings.Development of a pragmatic and easy-to-use tool that captures the best evidence on adherence and allows its application in the clinic setting.The study culminates in a pilot trial of the manualised intervention; a larger subsequent definitive trial is needed to test whether the intervention is efficacious and cost-effective beyond any initial conclusions regarding validity and feasibility derived from the pilot.

## Introduction

Against a background of rising tuberculosis (TB) in the 1990s and 2000s, the need for a comprehensive approach to TB control in England was deemed necessary by Public Health England and the National Health Service (NHS) England. In January 2015, these bodies jointly launched the ‘Collaborative Tuberculosis Strategy for England 2015–2020’.^1^ This seeks to reduce TB incidence, decrease health inequalities and ultimately contribute to international efforts to eliminate TB as a public health problem. Ensuring that people can take all of their medication as prescribed is one of the strategy’s priorities, as poor adherence to treatment for TB is a driver of worse patient outcomes,^2–9^ increases the risk of transmission (due to delayed sputum culture conversion)^10^ and can promote the development of drug resistance.^3 11–16^ Subsequent National Institute for Health and Care Excellence (NICE) guidance noted the lack of robust TB research in this area.^17^

Barriers to optimal adherence to treatment for TB may occur for a number of reasons. These include

Patient-related factors, including perceptions and beliefs.Cultural influences and current mental state.Structural economic factors and social support networks.Health service factors that include treatment complexity as well as accessibility of those services and the relationships patients develop with service providers.^18 19^

Non-adherence is not a single issue and may take various forms, for example, suboptimal implementation (skipping doses) or stopping treatment early (eg, as soon as a patient feels better.).^20^

Although a series of studies have been undertaken to define the population groups most at risk of non-adherence,^19^ it is currently difficult, prior to starting medication, to identify who may struggle with taking treatment as prescribed. To date, methods to support treatment address some, but not all, of the important underlying reasons for poor adherence. For example, the WHO’s recent focus on digital technologies reflects our attention on individual-level determinants of adherence and reminder/observation-based systems^21^; far less research has addressed the social and structural barriers to staying on TB treatment.

In the UK, the development of an intervention to support adherence to treatment that is sensitive to the individual’s cultural background and social circumstances, and can be routinely delivered within the NHS, is critical. To this purpose, a mixed-methods, patient-centred, approach to the study of the modifiable factors that influence patients’ adherence to treatment of TB is required.

## Methods and analysis

### Research question

Can a manualised package of intervention be developed to help overcome the social and cultural factors that lead to poor adherence to treatment in NHS patients in the UK with active TB?

### Aim

To develop, pilot and evaluate process and interim outcomes for an effective manualised intervention that improves the likelihood of adherence to treatment among NHS patients at risk of poor adherence due to social, cultural and structural factors.

### Objectives

Synthesise current knowledge on (1) determinants of adherence to treatment for TB and (b) interventions that can support adherence, with particular emphasis on social and cultural barriers (scoping review and conceptual framework).Apply a conceptual framework of adherence endorsed by NICE guidelines (the perceptions and practicalities (PAPA) approach)^18^ to elucidate and address the personal, sociocultural and health systems context, mechanisms and pathways of poor adherence among NHS patients with TB (formative research).Develop a manualised intervention (a series of systematic actions applied on the basis of a patient’s needs assessment) with multiple components that can identify (1) NHS patients most at risk of non-adherence, (2) the salient modifiable barriers and (3) the tailored support mechanisms required to meet individual patient needs by matching appropriate interventions to specific barriers, as recommended by NICE (Development of Intervention). A manualised intervention was considered to be a suitable approach to managing adherence in TB, as it will enable a set of measures to be applied consistently within different NHS settings that will aid both clinicians and patients throughout the treatment journey. The content of the intervention will use existing support measures, employed in a systematic and structured way, and may also include any new interventions that are developed in response to the formative research. It will be compared with normal care.Pilot the intervention package in people at risk of poor adherence to define how the components work in combination and separately (pilot study).Evaluate the process of implementation of this intervention through describing the challenges and facilitators in delivering the package as intended (fidelity and reach) and assessing the impact of the intervention through evaluation of adherence indicators (process evaluation).Use the findings of the pilot to assess the costs of delivering the manualised intervention in an NHS setting and to guide development of a proposal for a full randomised controlled trial (RCT).

## Study design

This study uses a mixed-methods approach. There are six subsections, reflecting the six objectives: (1) scoping review and conceptual framework, (2) formative research, (3) development of intervention, (4) pilot study, (5) process evaluation and (6) cost analysis and future work. Although the different elements are described separately further, the research activities for each will overlap, and some will run concurrently. The full programme of work and relationships between subsections is shown in figure 1. This paper reflects protocol V.4.0 (26 September 2019).^22^

**Figure 1 F1:**
[figure not shown]
IMPACT study. The six mixed-methods elements of the IMPACT study and the relationships between them. The study is guided by a steering group which has oversight over the entire process and culminates in a pilot study with associated evaluatory elements. IMPACT, Intervening with a Manualised Package to Achieve Treatment Adherence in People with Tuberculosis; NHS, National Health Service.

### Scoping review

To underpin the development of the manualised intervention, the first study subsection will undertake literature reviews to answer the following research questions:

What personal, social, cultural, health systems-related and structural factors affect individuals’ ability to adhere to treatment for TB?What kinds of intervention have been developed to address the multiple levels (personal, social, cultural, systems and structural) at which barriers to adherence may operate?What is the evidence for the successful impact of interventions to address barriers to adherence to treatment for TB?

These questions will be answered through the three following reviews:

A scoping review of qualitative studies that examine the personal, social, cultural, health systems-related and structural factors affecting adherence to treatment for TB from the perspectives of adult patients, caregivers or healthcare providers, as well as studies that evaluate interventions to support adherence to treatment for TB. Data from all settings will be considered, but with a particular focus on low incidence, high income settings.A critical review of quantitative studies examining the personal, social, cultural, health systems-related and structural factors affecting adherence to treatment for TB. This review focuses on low incidence, high income, settings and observational study designs. Given the scoping nature of the review, findings will be descriptively analysed and not be stratified or disaggregated, for example, by site of disease. All relative and absolute measures of effect will be extracted.A critical review of quantitative studies that have examined the effectiveness of interventions to improve adherence in people taking treatment for TB, building on existing systematic reviews, including the provision and delivery of information and/or education; enablers and/or incentives; social support; and case management approaches. Given the more limited literature, both observational studies and clinical trials will be included, from all settings. Findings will be descriptively analysed.

Together, these three reviews will enable us to conduct a critical interpretive synthesis of findings from qualitative and quantitative studies examining the assumptions and mechanisms of effect underlying interventions to improve adherence to treatment for TB. Further details on the reviews are available in the full protocol.^22^

### Formative research

#### Formative research methods, recruitment and eligibility

In line with findings from the scoping review, we will develop topic guides for qualitative interviews exploring current models of TB service delivery in the study sites, providers’ views on the barriers and facilitators for treatment adherence, and TB patients’ and their family members’ experiences of starting and staying on treatment. Details about these guides are available within the full protocol.^22^ The thematic analysis of these interviews will complement insights gained from the scoping reviews, which will allow us to refine a conceptual framework of adherence building on the PAPA.^18^ Approximately 50 participants will be enrolled.

Adults (aged 18 and over) who are currently taking or recently completed treatment will be identified by the local TB service at four UK sites (Southampton, Edinburgh, Central London and East London)) and will be asked to take part in the study. The services have been chosen for their patient diversity, geographical spread and as reflecting the national TB picture. The patient group will be enriched with people who have been poorly adherent to treatment, although we will also include patients who report full adherence so that we can capture what may have enabled them to take treatment as prescribed. With patient consent, family members and/or carers will also be approached and asked to participate.

Health and social care workers from both primary and secondary care settings will be directly approached by researchers and invited to be interviewed. All those approached will be aged 18 or over and involved in TB management and care.

#### Data collection methods

Three different methods of data collection will be used to undertake the formative research.

##### In-depth interviews: patients and family members/carers

These will be conducted as individual interviews with approximately 30 participants, using a topic guide. The areas to be explored are self-perception, personal beliefs and practices related to medicine-taking, health literacy and health-seeking behaviour, social support, cultural norms around health-seeking behaviour, and financial and other structural barriers.

##### Testing of Beliefs about Medicines Questionnaires (BMQ) and Brief Illness Perception Questionnaire (BIPQ) questionnaires with patients for their suitability

To ensure that the validated questionnaires (ie, 23BMQ and the 24BIPQ) are accessible and acceptable to patients, we will also conduct cognitive interviews with 10 patients. We will then have confidence to use them in the later pilot study to assess patient PAPA affecting adherence to anti-TB therapy. These will explore self-perception, personal beliefs and practices related to medicine-taking.

##### Semistructured interviews: healthcare providers

These will be undertaken with healthcare providers responsible for multiple aspects of TB care (doctors, nurses, social workers, directly observed therapy (DOT) providers, managers and administrators). They will focus on providers’ perceptions of factors affecting patient understanding of TB and its treatment, service delivery models including staffing, organisation of care and communication. We will interview four to six providers at each site, aiming for a total of 20 interviews.

We will use a framework approach^25^ to facilitate initial analysis of the interview transcripts. Short patient case studies will be created for each patient interview. Data on health systems issues gained through mapping patient pathways and provider interviews will be organised using a deductive approach, with appropriate visual pathways.

### Development of the manualised intervention

#### Intervention development process

The data collected from the scoping reviews and formative research will be presented to, and synthesised by, an intervention development group (IDG). A manualised intervention will be developed to identify (1) NHS patients most at risk of non-adherence, (2) their salient modifiable barriers and (3) the tailored support mechanisms that meet individual patient needs by matching appropriate interventions to these specific barriers.

The IDG will aim to include

Patients (in particular the homeless, ethnic minorities, migrants new to the UK, and patients with drug resistant TB).Family members/significant others of affected persons.Members of the public.Healthcare professionals (from both primary and secondary care).Other professionals who work with patients/communities affected by TB.

The constitution of the IDG will enable a coproduction approach to ensure that the intervention is pragmatic, can be delivered within the context of existing care pathways, and is of benefit to service users and those who are likely to access the intervention.

#### Intervention contents

The manualised intervention is likely to consist of a screening and assessment tool, in addition to a package of measures that can be tailored to the needs of individual patients from different population groups.

As patterns of adherence may be irregular over time, it is intended that the manualised intervention will be administered to all patients at each patient review. The tool thus needs to be quick and easy to administer. It may be electronically linked to patient records, enabling a comprehensive picture of the risk of possible non-adherence to be developed for each patient, as well as within a clinic population. The various delivery options for the intervention (such as using paper or an app) will be considered during its development stage.

The menu of supportive measures may, for example, include

Informational intervention: for example, providing a convincing story setting out the rationale and ongoing need for medication, addressing concerns about potential adverse effects and consequences of treatment and what to do if such events occur (eg, the participants will be informed that it is possible to change their treatment regimens to alternatives).^26^
Practicalities and capability-based interventions: video-observed therapy (VOT); DOT; reminders, including text messaging; automated methods for monitoring and feedback, including electronic dosette boxes; use of a medication app; incentives, for example, financial and food vouchers; mitigation; and management of drug toxicity due to treatments.Social and system interventions: offering flexibility in appointments; enhanced guidance on ‘navigating’ clinic pathways; signposting patients to relevant services, for example, housing, drug and alcohol services, and social care; and providing peer support.

### Piloting the intervention

#### Study design, recruitment and eligibility

Once the intervention is developed, proof of concept is required within the real world. This will be undertaken using a non-blinded cluster randomised pilot study that compares the manualised intervention to the usual standard of care in four London clinics treating TB. Two clinics will be randomly allocated to the intervention and two to standard of care. In the latter, the amount of support provided to patients is based on perceived need, as identified by a nurse-led review and a needs assessment. Most patients will have supported self-administered therapy, while others will be offered DOT and/or VOT if this is felt to be appropriate. We anticipate enrolment to commence in January 2020.

All consecutive patients aged 18 or over who are about to start treatment for TB, irrespective of the site of disease, will be approached to take part in the study. We will exclude individuals who are unable to provide informed consent, those already on treatment and those who are not expected to live for the duration of the study (a minimum of 6 months from starting treatment). Within the pilot study, it is essential to capture the entire treatment period for each patient in order to assess the effectiveness of the intervention. Due to the nature of the TB patient population in the UK, patients are likely to include people at greater risk of poor adherence, such as migrants newly arrived in the UK, people whose first language is not English, people with a mental health disorder, people taking immunosuppressive therapy or known to have immunodeficiency, those with a previous history of treatment for TB, or poor adherence with anti-TB medication, and people with a current or previous history of drug or alcohol misuse.

The purpose of the pilot study was not formal hypothesis testing. Given this, a target sample size of 80 patients enrolled (20 per site) was identified for the pilot study as providing useful information that can help determine whether the intervention will be deliverable within a clinical setting. It will also guide the development of a possible larger definitive study using the intervention. The four TB clinics of interest (in East and North London) each treat in excess of 60 relevant patients per annum.

Based on usage of DOT within the clinic populations seen at the treatment sites (ie, individuals currently identified as needing adherence support), we estimate that around 33% of patients will be at risk of non-adherence. Taking this as a minimum (as the manualised intervention is likely to be more sensitive than current risk assessments), we would expect that at least 26 of the 80 patients recruited will be identified as requiring adherence support. This sample size allows us to measure consent to enrolment for 80 individuals, data completeness for adherence and treatment outcomes for 80 individuals, data on acceptability and feasibility of the intervention package for around 40 individuals, and data on acceptability and feasibility of adherence support for at least 26 individuals (13 receiving the manualised intervention and 13 standard care).

#### Outcomes of the pilot

The primary outcome of the study will be level of adherence, measured as the proportion of prescribed doses taken and assessed at 6 months from the start of treatment. In addition to this primary outcome, a number of secondary outcomes will also be measured, as follows:

Proportion consenting to the study.Completeness of data for measures of adherence.Proportion of patients withdrawing during the study and the reasons why.Proportion of patients identified as needing adherence support in the intervention arm.Proportion of patients offered adherence support and accepting it in the intervention arm.Documentation of which adherence-promoting activities have been implemented among patients both in the standard of care and intervention arm, and when.Detailed treatment implementation information: for example, proportion of patients completing treatment, proportion of patients still on treatment after 9 months or at study completion (whichever is the earlier).Patterns of adherence (implementation and discontinuation).Impact of manualised intervention on maintaining adherence over the duration of treatment.Process variables: adherence-related PAPA.

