#### Analysis and interpretation

Where possible, univariable analyses will be undertaken to compare each outcome measure listed between study arms (intervention and control). For the primary outcome (adherence), the mean percentage value will be reported by arm (intervention and control) and histograms will be used to describe the distribution of values by study arm. Binary secondary outcomes will be reported by the proportion of individuals achieving the outcome within each arm. The need to adjust for clustering by site and clinical care provider will be assessed using the cluster summary method (a t-test) to compare the cluster means or proportions (as appropriate, between arms). An assessment of the balance in baseline characteristics between the study arms will also be conducted. If randomisation has failed to evenly distribute key characteristics (eg, age, sex, ethnicity or other factors identified as important during the scoping reviews), then the cluster means or proportions will be adjusted for these differences before applying the t-test. This two-stage approach to analysis is described by Hayes and Moulton.^31^ We recognise that adherence data may be highly skewed and thus may require compensatory analytical approaches.

The analysis of the first three of our secondary outcomes will address the feasibility of a definitive trial following a similar design to the pilot. Analysis of secondary outcomes 4–6 addresses the intervention, and complements the process evaluation (see below). Analysis of the primary outcome and final secondary outcomes around treatment adherence and completion provides initial information—given the modest sample size—concerning the effectiveness of the intervention, and may assist the sample size calculation for the definitive trial. They can also offer an alert in the unlikely event that the intervention is harmful.

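### Adherence is ranked as the sole primary outcome and feasibility outcomes go to a two-versus-two clinic comparison, in a pilot that disclaims hypothesis testing and sizes itself mainly on feasibility

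*Protocol article*

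**What the plan says.** All references are to the protocol article.

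- **Study design, recruitment and eligibility**, on purpose: "The purpose of the pilot study was not formal hypothesis testing". On size: "a target sample size of 80 patients enrolled (20 per site) was identified for the pilot study as providing useful information", information that can "help determine whether the intervention will be deliverable within a clinical setting". The same section adds that the pilot will guide a possible definitive study. It then lists what 80 patients allow to be measured: consent, completeness of adherence and outcome data, and acceptability and feasibility of the package and of adherence support. A between-arm adherence difference is not on that list.
- **Same section**, on allocation: "Two clinics will be randomly allocated to the intervention and two to standard of care".
- **Outcomes of the pilot**: "The primary outcome of the study will be level of adherence, measured as the proportion of prescribed doses taken", assessed at 6 months. Consent, completeness, withdrawal, need for support and uptake of support are secondary outcomes 1 to 5. Outcomes 4 and 5 are defined in the intervention arm only.
- **Analysis and interpretation**: where this can be done, "univariable analyses will be undertaken to compare each outcome measure listed between study arms". The only test named is a t-test on cluster means or proportions. Binary secondary outcomes are also to be reported as proportions within each arm. The section then says: "The analysis of the first three of our secondary outcomes will address the feasibility of a definitive trial". It describes the adherence result as initial information on effectiveness.
- **Power calculation**: Table 1 gives the power of the primary analysis with 40 patients per arm, for absolute increases in adherence of 10 to 30 points.

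**The concern.** Three parts of the plan pull apart. The statement of purpose rules out testing, and the 80 patients are explained by what they show about deliverability. The outcome ranking, the named test and the power table belong to an effectiveness trial.

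This has two practical consequences. First, the outcome that carries the label primary is the one the design informs least well. Second, the outcomes assigned to the feasibility of a definitive trial are sent to a comparison between arms. Whether a definitive trial can run depends mainly on the level reached (how many consent, how complete the data are, how many withdraw) and on how that level varies by clinic. A difference between two pairs of clinics does not estimate that level, and it is far less precise.

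**Working it through.** **Inputs from the article.** Four clinics, two per arm, 20 patients each; 80 in total, 40 per arm; cluster-level t-test; Table 1.

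**Assumptions, not in the article.** A feasibility proportion of 80%; ICC of 0 or 0.05; two-sided 5% level (not stated, but it reproduces Table 1).

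**1. The plan's own figure.** Table 1 reproduces as a comparison of two independent binary proportions, 40 per arm, pooled variance under the null, with no allowance for clustering. For 70% to 90%:

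- null SE = √(2 × 0.8 × 0.2 / 40) = 0.0894
- alternative SE = √((0.7 × 0.3 + 0.9 × 0.1) / 40) = 0.0866
- power = Φ((0.20 − 1.96 × 0.0894) / 0.0866) = Φ(0.285) = 0.61, as printed.

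All nine rows agree to within 1 percentage point.

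**2. The same scenarios under the named cluster-level test.** Degrees of freedom are 4 − 2 = 2, critical t = 4.30. Each clinic proportion has variance p(1 − p)(1 + 19 × ICC)/20. The SE of the difference is the square root of half the sum of the two arms' clinic variances. Power comes from the non-central t distribution.

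| Baseline to intervention | Table 1 | ICC 0 | ICC 0.05 |
|---|---|---|---|
| 70% to 90% | 0.61 | 0.27 | 0.17 |
| 70% to 100% | 0.98 | 0.59 | 0.38 |

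For 70% to 90% at ICC 0, SE = √((0.0105 + 0.0045)/2) = 0.0866 and the non-centrality is 0.20/0.0866 = 2.31. The 70% to 100% row is the most favourable in Table 1. These figures treat adherence as binary, as Table 1 does, although the analysis section reports a mean percentage.

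**3. Precision for a feasibility proportion of 80%.** Design effect at ICC 0.05 = 1 + 19 × 0.05 = 1.95.

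Overall level on 80 patients:
- ICC 0, normal: 1.96 × √(0.16/80) = 1.96 × 0.0447 = 8.8 points
- ICC 0.05, normal: 1.96 × √(0.16 × 1.95/80) = 1.96 × 0.0624 = 12.2 points
- ICC 0.05, t on 3 df (3.18): 3.18 × 0.0624 = 19.9 points

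Between-arm difference, t on 2 df:
- ICC 0: 4.30 × √(2 × 0.16/40) = 4.30 × 0.0894 = 38 points
- ICC 0.05: 4.30 × √(2 × 0.16 × 1.95/40) = 4.30 × 0.1249 = 54 points

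The like-for-like pair (ICC 0.05, t-based) is 20 against 54 points, a ratio of 2.7. A factor of 2 comes from estimating a difference rather than a level, and a factor of 4.30/3.18 = 1.35 from losing a degree of freedom.

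**4. Denominator for consent.** Consent is measured on patients approached, not on those enrolled. At 80% consent, 80 enrolled means 80/0.8 = 100 approached, 25 per clinic. With ICC 0.05 the design effect is 1 + 24 × 0.05 = 2.2. The level has half-width 3.18 × √(0.16 × 2.2/100) = 19 points and the difference 4.30 × √(2 × 0.16 × 2.2/50) = 51 points. The conclusion does not change.

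**The case against.** **The sample size is not explained by feasibility alone.** Correct. Guiding a definitive study is a second stated reason, and Table 1 gives power for an adherence effect with the same 80 patients. This narrows the point, but the power table also sharpens the conflict with the disclaimer of testing.

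**Not every outcome is compared.** Correct. The comparison is limited to where it is possible, and outcomes 4 and 5 exist in one arm only. Outcomes 1 to 3, the ones assigned to feasibility, carry no such restriction.

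**Effectiveness is among the aims.** Correct. The aim covers interim outcomes, an objective covers impact on adherence indicators, and the design section wants the whole treatment period captured so that effectiveness can be assessed. Collecting and reporting adherence is therefore justified. Ranking its contrast above all feasibility measures is not explained.

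**Levels are already reported, by arm.** Correct for binary outcomes, so the comparison does not replace all estimates. Intervals may well be left to the full protocol or analysis plan and are not counted as missing here. What this article does fix is a between-arm comparison for these outcomes.

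**A difference between arms can matter for feasibility.** Fair. In an unblinded cluster design with individual consent, differential consent or withdrawal is a real concern. Values by arm should be shown, but a test on 2 df will not settle the question.

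**Stronger readings that the article does not support.** A reader might infer that the pilot cannot serve its purpose, that it plans an efficacy claim, or that a go/no-go decision hangs on the primary result. The article calls the adherence result initial information, says a larger trial is needed to test efficacy, and bases the final package on the process evaluation and the experience of piloting. No section links a decision to the primary outcome. Progression values may stand in the full protocol, so their absence from this condensed article is not a finding.

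**Conclusion.** The concern holds as one of ranking and choice of contrast. The article disclaims hypothesis testing and lists feasibility quantities as what 80 patients can measure, then makes adherence the only primary outcome, names a test and gives its power. The outcomes it assigns to feasibility are routed to a two-versus-two clinic comparison that is about 2.7 times less precise than the overall level: 54 against 20 points at an assumed 80% and ICC of 0.05. Across the assumptions used, the range is 38 to 54 points for the difference and 9 to 20 points for the level; the 9 ignores clustering and is not a like-for-like comparator. Under the named cluster-level test, power for adherence is at most 0.59 in any Table 1 scenario, even with no between-clinic variation.

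The ICC and the 80% are assumptions, since the article gives neither. The internal inconsistency does not depend on them. It is worth correcting, but it does not invalidate the pilot: feasibility outcomes are listed and adherence data remain useful for planning the definitive trial.

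**What to change.** - **Outcomes of the pilot:** make the feasibility outcomes already listed primary, namely consent, completeness of adherence data, withdrawal, and, in the intervention arm, need for and uptake of support. Make adherence exploratory.
- **Analysis and interpretation:** report secondary outcomes 1 to 3 as an overall level with a 95% interval that treats clinic as the cluster, together with the four clinic values. Values by arm may be shown descriptively, to reveal differential consent or withdrawal, without a test. Report adherence by clinic and arm as an estimate with a cluster-level interval and no p-value.
- **Power calculation:** remove Table 1, or restate it for two clinics per arm with the assumed ICC given.

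The cost is wording only, with no extra patients or data. The downside is that the pilot gives up a formal between-arm test of adherence.
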